#### Sample size of cases

The sample size of 4100 study participants anticipated in the intervention arm (Ife North LGA) will include both asymptomatic (40–70 years) and symptomatic (30–70 years) women that will undergo screening and diagnostic evaluations respectively. In any screening exercise, there will be symptomatic cases that will use the opportunity of screening to present for evaluation. We anticipate a CDR of at least 3.5%. This expectation is supported by our previous publication of a mixed screening and diagnostic population in this geographic region demonstrating a breast CDR of 3.5% [19]. The CDR in this study will be the number of cancers detected among all study participants, including both the symptomatic and screening arms.

Our previous data demonstrate that the mean breast tumor size from an entirely symptomatic population at OAUTHC was 10.5 cm. This is much larger than findings from our recent study from the same region which included a screening population which demonstrated an average breast cancer size of 3.3 cm [19, 22]. We therefore project that cancers in the intervention community will be follow a similar pattern.

The primary outcome measure in this study is the stage at diagnosis. To achieve this, we projected the number of cases needed to detect a difference in the proportion of cases based on stage at diagnosis between the two study arms. From our preliminary data of 25 staged cancers, there were 7 (7/12, 58.3%) and 2 (2/13, 15.38%) stage IV cancers in the control and intervention arms respectively, with a 43% difference between the two groups. In order to detect a 43% difference in stage IV diagnoses between the two study arms with 80% statistical power at an alpha of 0.05, 23 cases will be needed in each arm. Our preliminary data show 13 total cancer cases detected in 791 patients and 12 total cancer cases detected in 82 patients in the intervention and control arms, respectively, in the first year. Going by this annual accrual rate, in two years, there should be 26 cancer cases out of 1582 patients in the intervention arm and 24 cancer cases out of 164 patients in the control arm. Therefore, achieving the 23 cases required for statistical significance in the stage at diagnosis in each arm at the end of the 2-year study period is possible.

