#### Control arm

The control LGA is about 4 kilometers from OAUTHC which is the referral tertiary hospital in this study. There are radiological (including ultrasound, mammography, computerized tomography, and magnetic resonance imaging services), pathological and surgical specialty services for breast cancer within OAUTHC which is also the primary institution of the study’s principal and co-investigators in Nigeria. In the control LGA, awareness creation will follow a similar procedure as outlined above for the intervention LGA. No other intervention will take place in the control arm. Women will not be invited to participate in a screening program and there is no community-based imaging, biopsy, or navigation. Women are expected to present to the PHCs if they have breast complaints which is a routine practice. Management of patients with breast-related complaints will be based on the current standard of care which is a review by the CHNs who refer or clinically manage otherwise based on his/her assessment. Twice a month, research staff will visit the selected PHCs in the control LGA to obtain data on the number and records of breast-related cases seen at the PHCs and those referred to OAUTHC. Patients referred to OAUTHC for suspicion of breast cancer will be tracked to determine the stage at diagnosis and the timelines from presentation at the PHC to eventual treatment at OAUTHC. In addition, patients presenting directly to OAUTHC from the LGA based on self-referral will also be identified and their data obtained.

Although the control arm participants do not have intervention provided in their LGA, they however get same workup, management and are navigated along the same pathway as the intervention arm participants once they present in OAUTHC for screening and diagnostic evaluation.

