Participation rate: This will be determined by calculating the percentage of women screened/evaluated of the total number of eligible women based on census data. A participation rate of 70% will be considered satisfactory in the intervention arm. The number of screened/evaluated women in the intervention and control arms will also be compared.Cancer detection rate (CDR): This refers to the number of histopathologically diagnosed cases of breast cancer per 1,000 evaluated populations in both screening and diagnostic groups. This will be compared between the control and intervention arms.Timeline from presentation to treatment: The time interval between presentation for breast evaluation and treatment in OAUTHC of the cases in the two arms will be compared.Retention rate: The retention rate refers to the number of women who return for repeat annual screening of the total initial number of women initially screened in the first year. A repeat screening within a year and a half will be considered acceptable for this two-year study. To ensure all accrued participants get their second screen, we will follow them up beyond the initial study period as needed.Abnormal call rate: This is defined as the number of women with abnormalities detected on iBE and/or CBE requiring further evaluation either by imaging with or without biopsy out of the total number of asymptomatic and symptomatic without an obvious lesion participating in the study. There are 2 groups of participants (diagnostic and screening) in each of the 2 arms (intervention and control). The screening group constitutes the asymptomatic participants while the diagnostic group constitutes the symptomatic participants. The interventions in this study include enhanced CBE (CBE + iBE), community-based diagnostic evaluation (with portable ultrasound and mobile mammography), and biopsy (if warranted). To evaluate which of CBE and enhanced CBE was of greatest value, another layer of analysis will be provided to address this question by comparing the concordance of the two with imaging which is the gold standard. This study also provides an additional opportunity to evaluate the iBE device.

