### Statistical analyses

All data entered into the REDCap database will be exported as a dataset into R 4.2. Sociodemographic characteristics of the participants will be assessed using medians and interquartile ranges (IQR) for continuous variables and counts and percentages for categorical variables. Participation rate, retention rate, abnormal call rate, rate of late-stage diagnosis, and CDR will be reported as proportions with 95% exact confidence intervals. As for late-stage diagnosis, stage 4 cancers will be considered late-stage. The above-mentioned metrics will be compared between the intervention and control arms using Chi-square tests or Fisher’s exact test. The time intervals from presentation to treatment will be reported using medians and IQR and will be compared between the intervention and control arms using the Wilcoxon rank-sum test. The rate of late-stage diagnosis will be estimated and compared between the intervention and control arms on a yearly basis, starting from baseline, to assess if the intervention arm shows betterment in this rate consistently. Bonferroni correction for type I error will be implemented (α* = 0.0167) for this comparison. A logistic regression analysis which accounts for the ward (random effect) in which the patient was examined will also be performed with late-stage diagnosis as the dependent variable and time of screening, the interaction between the allocated groups (intervention and control arms), and time of screening as the independent variables. For all statistical comparisons (other than the one mentioned immediately above), the type I error rate (α) will be set to 0.05. All statistical analyses will be conducted using R 4.2 software [24]. Sample size calculations were done using the clinfun package of the R 4.2 software [25].

We do not anticipate any missing data due to loss of follow-up because the research team will make every effort to retain recruited participants. However, if missing data issues do arise, we will implement multiple imputation techniques, which impute missing data under the missing at random (MAR) assumption. Sensitivity analysis of the findings after multiple imputations will thereby be performed and these findings will be compared to those obtained from complete case analyses.

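### The planned between-arm test of cancer detection rate per evaluated woman compares differently selected denominators, and retention and abnormal-call rate have no comparable control-arm procedure

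*Protocol article*

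**What the plan says.** - **CDR.** The secondary outcomes (Program evaluation and outcome measures) define CDR as histologically diagnosed breast cancers per 1,000 evaluated, over the screening and diagnostic groups together, and add: "This will be compared between the control and intervention arms".
- **Test.** Statistical analyses names five proportions, CDR, retention and abnormal-call rate among them, and continues: "The above-mentioned metrics will be compared between the intervention and control arms using Chi-square tests" or Fisher's exact test, at alpha 0.05.
- **Control arm.** "Women will not be invited to participate in a screening program and there is no community-based imaging, biopsy, or navigation". Women there are expected at the primary healthcare centre (PHC) if they have breast complaints. Self-referrals to the teaching hospital (OAUTHC) are also captured.
- **First-year yield** (Sample size of cases): "13 total cancer cases detected in 791 patients and 12 total cancer cases detected in 82 patients in the intervention and control arms", respectively.
- **Retention and abnormal-call rate.** Retention is return for repeat annual screening among women screened in the first year. An abnormal call is a positive iBE and/or CBE needing further evaluation. The same section says that each arm has a screening and a diagnostic group.
- **Time to treatment.** It runs from presentation for breast evaluation to treatment at OAUTHC. "The time intervals from presentation to treatment will be reported using medians and IQR and will be compared" by the Wilcoxon rank-sum test. If data are missing, multiple imputation under missing at random (MAR) is planned, set beside complete-case results.

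**The concern.** A detection rate per evaluated woman depends on the case mix of the women evaluated. An arm that invites asymptomatic women adds many without cancer to its denominator; an arm that sees women with complaints does not. The more women the programme reaches, the lower its CDR can fall against control, however many cancers it finds. The Aims list CDR among the measures of the programme's impact, so a highly significant difference would be reported for a named impact measure when it chiefly describes recruitment.

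Retention and abnormal-call rate raise a related problem. Annual recall, CBE training and iBE are described only for the intervention arm, yet both rates are on the list to be tested between arms.

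Time to treatment, one of the two measures by which the abstract judges impact, needs the same start in both arms and a rule for women not yet treated.

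**Working it through.** **Inputs.** From Sample size of cases: 13/791 and 12/82 in year 1; 26/1,582 and 24/164 projected at two years; target of 4,100 women and CDR of 3.5%. From Sample size of study participants: 5,800 and 4,500 women aged 40–70 in the selected wards.

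**1. The plan's own figures.** The two-year counts are the first-year counts doubled: 2 × 13 = 26, 2 × 791 = 1,582, 2 × 12 = 24, 2 × 82 = 164. The primary-outcome sample size also reproduces. With stage IV rates of 7/12 and 2/13, two-sided 5% (sidedness is not stated; assumed), 23 cases per arm give exact Fisher power of 81.4%, and 22 give 78.6%. That calculation counts cancer cases, so nothing below touches it.

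**2. CDR as defined.** CDR = cases / evaluated × 1,000, with exact 95% intervals.

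| | Intervention | Control | Fisher p |
|---|---|---|---|
| Year 1 | 13/791 = 16.4 (8.8 to 27.9) | 12/82 = 146.3 (78.0 to 241.7) | 4.1e-7 |
| Two years, projected | 26/1,582 = 16.4 (10.8 to 24.0) | 24/164 = 146.3 (96.1 to 209.9) | 6.5e-13 |

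The control rate is 146.3 / 16.4 = 8.9 times the intervention rate.

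**3. If recruitment reached its target.** 4,100 × 0.035 = 143.5, say 144 cancers, or 35.1 per 1,000. Against the projected 24/164 = 146.3 per 1,000, Fisher p = 1.3e-8, still lower in the intervention arm.

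**4. Where the gap comes from (illustrative).** On the ward populations:
- Evaluated: 791/5,800 = 13.64% and 82/4,500 = 1.82%, a ratio of 7.48.
- Cancers, year 1: 13/5,800 = 2.24 and 12/4,500 = 2.67 per 1,000, control 1.19 times higher, Fisher p = 0.69.
- 7.48 × 1.19 = 8.9, the whole CDR ratio. Most of it is the difference in how many women were evaluated.
- Cancers, two years: 26/5,800 = 4.5 and 24/4,500 = 5.3 per 1,000, p = 0.57.
- At the recruitment target: 144/5,800 = 24.8 against 5.3 per 1,000. The direction is opposite to step 3 on the same cancers.

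These re-based rates put all cases over women aged 40–70 in the selected wards. Cases may include symptomatic women aged 30–39, and control self-referrals are identified from the LGA. The rates show the mechanism; they are not estimates of effect.

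**5. Retention and abnormal-call rate.** No arithmetic applies. The annual repeat visit and the trained CBE and iBE examination appear only in sections headed for the intervention arm. Control arm allows awareness creation and no other intervention. The secondary outcomes nevertheless place a screening group in both arms, and Control arm mentions women presenting at OAUTHC for screening. The passages do not fit together.

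**6. Time to treatment.** The secondary outcomes give one start for both arms, presentation for evaluation. Control arm speaks of presentation at the PHC for referred women; self-referred women first present at OAUTHC. Read as first presentation at either place, the definition covers both routes.

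**The case against.** **Every metric here is secondary, and the primary is unaffected.** This stands. Stage at diagnosis has cancer cases as its denominator. But CDR is among the Aims' impact measures, and its test is fixed in the text.

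**The protocol predicts no direction for CDR, and nothing gives the symptomatic share of the 791 or the 82.** Also true. A reader might infer that the test would show harm; the documents do not call a low CDR harm, and the ward-based first-year rates are slightly lower in the intervention arm too. The point needs only that the two groups are selected differently, which the recruitment rules establish.

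**Retention and abnormal-call tests are possible.** A reader might infer that they cannot be computed. The documents do not support that: both groups are said to exist in both arms, and an abnormal call may rest on CBE alone. Non-comparable is the accurate word.

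**The time comparison is sound as defined.** A reader might infer that the arms run on different clocks, that monthly imaging visits bias the result, or that untreated women are dropped. None of this is supported. One definition serves both arms, the imaging wait is part of the pathway being evaluated, and the text does not restrict the Wilcoxon test to treated women. What remains is that the MAR fallback, if applied to women who have not started treatment, would give them treatment times; their times are censored, not missing.

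**Conclusion.** The concern holds for CDR and is worth correcting before analysis. As written, the plan tests a rate that differs 8.9-fold on the protocol's own counts (p = 4.1e-7 in year 1, 6.5e-13 projected) and would still be significantly lower in the intervention arm at full recruitment. The conclusion rests on the stated recruitment rules and on the projected control counts being borne out. The attribution to denominators rests on the illustrative ward populations.

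For retention and abnormal-call rate the conclusion is weaker: the control arm has no comparable procedure, and the sections disagree about whether it has a screening group. For time to treatment it is weaker still: the definition is usable and needs applying uniformly, with censoring.

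**What to change.** 1. **CDR.** Remove it from the list of proportions tested between arms. Report it within each arm with exact intervals, split by screening and diagnostic group. If arms are compared, use detected cancers per 1,000 eligible resident women, matching cases and population on age and ward: for example, cases aged 40–70 living in the selected wards over 5,800 and 4,500. Including cases aged 30–39 would need a population count for that age band, which the article does not give.
2. **Retention and abnormal-call rate.** Reconcile Control arm, the secondary outcome definitions and Statistical analyses on whether controls have a screening group. Report both rates for the intervention arm with exact intervals and no between-arm test.
3. **Time to treatment.** State that the start is first presentation for evaluation, at a PHC or OAUTHC, in both arms. Show results by referral route. Treat women not yet on treatment as censored instead of imputing times under MAR.

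**Cost.** Mostly wording. Ward of residence must be recorded for self-referred cases; the planned address check is at LGA level. The between-arm p-values given up for CDR, retention and abnormal-call rate are not interpretable.

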## Introduction

Breast cancer is a major public health challenge in Nigeria with an incidence of 52/100,000 [1], three-fold higher than the incidence four decades ago. Breast cancer incidence is projected to continue to increase in the coming decades. More worrisome, however, is the pattern of presentation–up to 80% of breast cancer cases in Nigeria present in advanced stages [2, 3]. This contributes significantly to high breast cancer mortality rates. This pattern of late presentation has remained unchanged over the last three to four decades [4]. Consequently, when combined with limited access to treatment overall, breast cancer survival in Nigeria is poor compared to high-income countries (HICs) [5–7]. Given the projected rise in breast cancer incidence, there may be an epidemic of advanced breast cancer cases without effective intervention in the coming years [8]. In addition to some recognized biological factors accounting for aggressiveness, it is clear that correctible epidemiological and system-related factors play major roles in late-stage presentation [9]. Both patient and system-related factors contribute significantly to delayed presentation [10]. Delayed presentation and lack of access to diagnostic and treatment facilities are recognized principal factors accounting for poor outcomes in low-middle-income countries (LMICs) [11, 12]. Patient-related factors include lack of breast cancer knowledge, fear of a cancer diagnosis and treatment, use of traditional and alternative remedies, and financial constraints. Awareness creation, community education, and advocacy to address erroneous patient beliefs must therefore form the basis of any early detection program. In addition, a lack of accessible breast cancer screening and the absence of a clearly defined clinical pathway for evaluating women with breast masses, coupled with limited access to diagnostic and treatment facilities, are key system factors requiring intervention [13].

Currently, there are no local data to support a specific breast cancer screening model in Nigeria. Developing a successful breast cancer screening program in a resource-limited setting requires substantial logistical and cultural considerations. Although mammography is recommended as the gold standard based on data from HICs, there are personnel, financial, and infrastructural challenges that limit its applicability for routine use in Nigeria [14].

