### Patient navigation and follow-up in the intervention arm

Patients with histologically confirmed breast cancer will be scheduled to visit the next available breast clinic at OAUTHC. Navigation to the breast clinic will be facilitated by the CHNs after the Radiologists have communicated the biopsy results to both the patient and the nurse (Fig 3). The CHNs will also check in with the patients regularly on weekly basis through phone calls and/or home visits to ensure they comply with their appointments and follow treatment recommendations. Each patient will have a Case Report Form (CRF) (S4 File) which contains the socio-demographic and clinical data; CBE, iBE, and imaging (ultrasound and mammography) findings; pathology diagnosis (histopathology and immunohistochemistry) and treatment data. The socio-demographic and clinical data, CBE, and iBE sections of the CRF will be filled out for the study participants by the trained CHNs while the imaging, pathology, and treatment sections of the CRF will be filled out by the research study assistants (RSAs). The filled CRFs at the three PHCs will be collated and transferred to OAUTHC by the RSAs who visit the PHCs on weekly basis to monitor recruitment activities and collect paper data records for upload to REDCap in OAUTHC.

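### Time to treatment is compared only among women who start, so a difference in treatment uptake cannot show and may be hidden

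*Protocol article*

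**What the plan says.** The outcome is defined under Program evaluation and outcome measures, among the secondary outcomes: "The time interval between presentation for breast evaluation and treatment in OAUTHC of the cases in the two arms will be compared". Statistical analyses fixes the method: "The time intervals from presentation to treatment will be reported using medians and IQR", and the intervals "will be compared between the intervention and control arms using the Wilcoxon rank-sum test".

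The same section has one provision for absent values: "if missing data issues do arise, we will implement multiple imputation techniques, which impute missing data under the missing at random (MAR) assumption". As a sensitivity step, "these findings will be compared to those obtained from complete case analyses". No censoring rule, competing event or not-treated category is given. The share of cases who start treatment is not among the listed outcomes.

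Two other places bear on who will lack an interval. The Introduction lists among the local barriers "fear of a cancer diagnosis and treatment, use of traditional and alternative remedies, and financial constraints". Patient navigation and follow-up in the intervention arm has the nurses contact patients weekly "to ensure they comply with their appointments and follow treatment recommendations".

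**The concern.** The interval exists only once treatment has begun. A woman with confirmed cancer who declines, defaults or dies first has no start date at all. One diagnosed late in the two years may still be waiting, so her interval is known only to exceed her follow-up. The article extends follow-up only to complete second screens. A median and a rank test on observed intervals leave out all of these women.

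This would matter little if starting treatment were unrelated to arm. Here navigation in the intervention LGA is intended to change it, so the analysis conditions on an event that lies on the programme's own pathway. If more intervention cases start, that benefit has no place in the result. If the additional starters are also slow, they lengthen the intervention median while the corresponding control women are absent, and the programme can look slower because it reached them.

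The sensitivity step would not reveal this. Complete-case analysis drops the women. Within-arm imputation under MAR draws their times from those of starters, so the expected medians do not move.

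**Working it through.** **The plan's own figures.** The article gives no power or sample size for this outcome. Its case projection doubles first-year counts: 13 × 2 = 26 intervention and 12 × 2 = 24 control. The 23 cases per arm required for stage IV (7/12 v 2/13, 80% power, alpha 0.05) is reproduced: exact Fisher power is 78.6% at 22 per arm and 81.4% at 23.

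**Inputs.** From the article: 24 control and 26 intervention cases, and a Wilcoxon test at 0.05. Assumed, because the article gives nothing: the never-treated share p in each arm, and exponential times with a 60-day median among starters in both arms.

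**All-case median.** With a share p never treated, the proportion started by day t is (1 − p)(1 − 2^(−t/60)). Setting this to 0.5 gives t = 60 × log2[1 / (1 − 0.5/(1 − p))].
- p = 0.1: 70 days
- p = 0.2: 85 days
- p = 0.3: 108 days
- p = 0.4: 155 days

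Among starters only, the true median is 60 days whatever p is.

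**Rejection rates** (simulation, at least 4,000 trials per scenario):

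| Never treated, control v intervention | All-case median, days | Starters-only Wilcoxon | Non-starters ranked last |
|---|---|---|---|
| 15% v 10% | 77 v 70 | about 5% | about 6% |
| 20% v 10% | 85 v 70 | about 5% | about 9% |
| 30% v 10% | 108 v 70 | about 5% | about 23% |
| 40% v 10% | 155 v 70 | about 5% | about 46% |

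The planned test stays at its nominal level however far uptake differs.

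**When the direction can reverse.** Suppose 30% of controls never start, and the corresponding 30% in the intervention arm all start, but after day 120. Mean starters-only medians are then about 62 days (control) and 106 days (intervention). The planned test declares the intervention slower in about 23% of trials and faster in about 0.1%. Before day 120 the all-case curves are identical:
- started by day 60: 0.7 × 0.5 = 35% in each arm
- started by day 90: 0.7 × (1 − 2^(−1.5)) = 45% in each arm
- all-case median: 108 days in each arm

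Only the later proportion separates the arms: 70% v 100% by the end. Early fixed times and the median would miss this benefit too.

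**Other distribution.** Log-normal times (median 60 days, log-SD 0.6), with the median of the additional starters varied:

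| Uptake, intervention v control | Median of additional starters | Starters-only: declared slower | Ranked last: declared better |
|---|---|---|---|
| 90% v 90% | none | about 2.5% | about 2.5% |
| 90% v 70% | 60 / 120 / 180 days | 2% / 10% / 14% | 22% / 10% / 9% |
| 90% v 50% | 60 / 120 / 180 days | 3% / 23% / 40% | 70% / 42% / 31% |

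With equal uptake and timing the two analyses agree and there is no bias.

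**The case against.** **The outcome is secondary.** Program evaluation and outcome measures presents time to treatment as groundwork for later studies, and the sample size rests on stage alone. This stands and limits the severity. The Abstract does, however, name the treatment timeline beside stage as a measure of the programme's impact, so the outcome is not trivial.

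**The uptake gap may be small.** The Control arm section says control women follow the same navigation pathway once they reach OAUTHC, and their LGA is about 4 km away, against about 25 km for the intervention LGA. Both facts may narrow the gap. The same section says there is no community-based navigation in the control LGA, so a gap remains plausible. At modest gaps the better test gains little power, although the uptake shares would still inform.

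**A reader might infer that women known to be untreated will be given an imputed treatment date.** The article does not say so. Its missing-data paragraph is framed around loss to follow-up, and Data collection and management has referred women tracked to the final point of care, so a known non-starter is not lost. What can be said is that no other rule is stated.

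**A reader might also infer that the plan will make a working programme look harmful.** That needs the additional starters to be slower as well as more numerous, and nothing in the article shows that they will be.

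**The detail could sit in an analysis plan.** The article itself fixes the summary and the test, and these do not fit the outcome. That is a stated choice rather than an omission.

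**Conclusion.** The point holds as one that should be fixed, for a secondary outcome. As written, the comparison is in effect restricted to starters and cannot show a difference in treatment uptake. If uptake differs between arms, the benefit may be hidden; if the additional starters are also slower, the direction may reverse.

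The size cannot be stated from the article. The illustrations rest on assumed never-treated shares and a 60-day median among starters. They run from almost no practical difference between the tests (about 6% v 5% rejection at 15% v 10% never treated) to a large one (46% v 5% at 40% v 10%). With no non-starters, or with equal uptake and timing, there is no between-arm bias. The documents do not support calling this a threat to the trial's main conclusion: the stage comparison and its 23 cases per arm do not depend on it.

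**What to change.** In the secondary outcome definition and in Statistical analyses:

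- Analyse all histologically confirmed cases in both arms as time from presentation to first treatment.
- Censor women still untreated at last contact or at a common cutoff, and treat death before treatment as a competing event.
- Compare arms with Gray's test or a log-rank test. With about 25 cases per arm, a rank test placing non-starters last is a simpler alternative.
- Report by arm the proportion ever started by the end of follow-up, and the proportion started by fixed times that include a late one.
- State that no start date is imputed for a woman known to be untreated.
- Keep the starters-only median and IQR as a descriptive figure.

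The cost is analysis wording. Treatment information is already collected for referred women, and the project is still in its implementation phase. The downside is that a median may not be reached in an arm with many non-starters.

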A descriptive analysis of the data will be done at 1.5 years for the retention rate and abnormal call rate to inform our decision for future investigations. The rate of late-stage diagnosis will be estimated on a yearly basis. However, no stopping rules will be employed. This estimation will purely serve the purpose of detecting any difference in the annual trends of the stage of diagnosis over time between the intervention and control arms.

The initial findings for the subset of women who undergo a second round of screening will be examined to identify the stage of presentation in this group of women if diagnosed during the second round. Given in our setting ~80% of patients with breast cancer present in stages 3 and 4, we expect to see a trend toward earlier stage of presentation (stages 0, 1 and 2) in women undergoing repeat breast evaluation.

The 2-year study period is enough to generate adequate data to measure the participation rate and difference in stage at diagnosis between the study arms, as elaborated in the sample size calculation of the cancer cases. In addition, this study will provide a groundwork for exploring the difference in CDR between the 2 modalities (CBE and enhanced CBE) and the time to treatment, generating data to guide future studies in our population.

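### The yearly late-stage tests aim to show consistent benefit but use a fixed Bonferroni threshold suited to an any-year claim; the decision rule should be stated and the correction matched to it

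*Protocol article*

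**What the plan says.** The Statistical analyses section compares the late-stage rate (stage 4) between arms every year, beginning at baseline, to see whether the intervention arm shows "betterment in this rate consistently. Bonferroni correction for type I error will be implemented (α* = 0.0167) for this comparison". For other comparisons, "the type I error rate (α) will be set to 0.05". The named tests are chi-square or Fisher's exact.

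Program evaluation and outcome measures describes the same yearly look: "The rate of late-stage diagnosis will be estimated on a yearly basis". It adds "However, no stopping rules will be employed" and then "This estimation will purely serve the purpose of detecting any difference in the annual trends of the stage of diagnosis over time" between the arms.

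The yearly numbers come from Sample size of cases, which reports "13 total cancer cases detected in 791 patients and 12 total cancer cases detected in 82 patients" (intervention and control respectively) in the first year. Its stage IV proportions are 7/12 (58.3%) in the control arm and 2/13 (15.38%) in the intervention arm.

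No section says what pattern of yearly results would count as consistent betterment.

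**The concern.** Doing better consistently is, on its ordinary meaning, a claim about all the years together. Bonferroni is built for the opposite kind of claim, where one significant result among several is enough and the chance of at least one false positive has to be held down. The aim and the correction therefore point to different decision rules, and the text settles on neither.

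The choice matters because each year brings only 12 or 13 cases per arm. A stricter threshold at that size costs a good deal of power. If the intended claim is benefit in every post-baseline year, the plan pays that price for protection that the claim already has. If the intended claim is benefit in some single year, the protection is needed but can be had at a lower price.

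**Working it through.** **Reproducing the plan's figures.** 0.05/3 = 0.0167, so three comparisons are being counted; baseline, year 1 and year 2 is the natural reading of a two-year study that starts from baseline. The plan's 23 cases per arm also reproduces: an exact two-sided Fisher test at 58.3% v 15.4% has power 78.6% with 22 per arm and 81.4% with 23. Sidedness is not stated; two-sided is assumed here and is consistent with the 23.

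**Inputs.** Control: 12 cases a year, stage IV probability 7/12. Intervention: 13 cases a year, probability 2/13. Yearly cohorts are taken as separate and independent unless stated otherwise.

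**Power in one year.** Sum Bin(x; 12, 7/12) × Bin(y; 13, 2/13) over all tables where the two-sided Fisher p-value is at or below the threshold and the intervention arm has the lower rate:

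- threshold 0.05: 60.8%
- threshold 0.025: 43.2%
- threshold 0.0167: 40.7%

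**Reading A: benefit in every post-baseline year.** The joint claim is false if at least one year has no benefit. Then P(all years reject) ≤ P(that year rejects) ≤ the per-year threshold. So 0.05 per year already caps the joint error at 5%, and 0.0167 caps it at 1.67%. In the worst case (no effect in one year, certain success in the other), Fisher's benefit-direction error with these numbers is at most 2.2% at 0.05 and 0.6% at 0.0167.

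Chance of succeeding in both years:

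- at 0.05: 0.608² = 37.0%
- at 0.0167: 0.407² = 16.6%, a ratio of 0.45

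Sensitivity of that ratio:

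- uncorrected chi-square: 40.9% v 18.7%, ratio 0.46
- 12 v 12 cases with uncorrected chi-square: 40.7% v 21.3%, ratio 0.52
- cumulative data (12 v 13, then 24 v 26) by Fisher: 59.4% v 38.7%, ratio 0.65

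**Baseline.** The Primary outcome measures text expects late-stage numbers to be high at first and to fall later. With 58.3% in both arms at baseline, Fisher rejects in the benefit direction 1.9% of the time at 0.05 and 0.5% at 0.0167. An all-three rule would then succeed with probability 0.0189 × 0.370 = 0.7% at 0.05, and 0.00525 × 0.166 = 0.09% at 0.0167. Dropping Bonferroni would not rescue a rule that includes baseline.

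**Reading B: any single year may be claimed.** Three unadjusted independent tests have familywise error 1 − 0.95³ = 14.3%. At 0.0167 it is 1 − (1 − 0.05/3)³ = 4.9%. A correction is needed.

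Holm compares the smallest p-value with 0.0167, the next with 0.025 and the largest with 0.05. Write A = 0.4319 for P(p ≤ 0.025), b = 0.4319 − 0.4075 = 0.0244 and c = 0.6082 − 0.4319 = 0.1763.

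- All three significant, full effect at each: (A³ + 3A²c) − (b³ + 3b²c) = 17.9%, against 0.4075³ = 6.8% at fixed 0.0167.
- Both post-baseline years significant, three tests in the family, no effect at baseline: 18.8% against 16.6%.
- Family of the two post-baseline tests only: A² + 2Ac = 33.9%, against A² = 18.7% for Bonferroni at 0.025.

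**The case against.** The strongest reply is that nobody wrote an every-year rule. Consistency can describe a pattern read off separate yearly results, and the phrase about any difference in annual trends in Program evaluation and outcome measures fits judging each year by itself. Under that reading a correction is needed. This stands. A reader might infer that Bonferroni here buys nothing, or that it more than halves the chance of success as a matter of fact. The documents do not support either without conditions: the first needs the every-year reading, and the second also needs separate yearly cohorts.

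A reader might also infer that 0.0167 misstates the error rate of the claim. It does not; the text labels it as a Bonferroni-corrected level for this comparison, not as the error of a joint claim.

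It can further be said that low power comes mainly from 12 or 13 cases a year. That is right: at 0.05 the every-year claim is still missed 63% of the time. The correction makes this worse but is not the root of it.

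Finally, a fixed threshold can be applied as each year's result arrives, whereas Holm needs all the p-values. That is a real convenience, but with no stopping rules nothing in the trial depends on an early yearly verdict. The correction errs on the conservative side and does not touch the end-of-study comparison. The planned logistic model with a group-by-time interaction also addresses change over time. These points limit the seriousness; they do not reconcile the aim with the correction.

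**Conclusion.** The point holds in conditional form. The stated aim and the stated correction do not match, and no decision rule links them.

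- If the claim is benefit in every post-baseline year, no correction is needed, and 0.0167 lowers the chance of showing it from about 37% to 17%. This assumes two separate cohorts of 12 v 13 cases, the planning rates of 58.3% v 15.4%, and two-sided Fisher tests. With cumulative data the fall is from 59.4% to 38.7%.
- If the claim is benefit in any single year, a correction is right, but Holm has the same familywise control and is never less powerful. The gain ranges from small (about 19% v 17% for both post-baseline years when baseline shows no effect) to large (about 18% v 7% for all three when the full effect holds at each).

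On either reading, fixed 0.0167 is not the best choice. This is an inexpensive improvement to a supporting analysis, not a threat to the end-of-study comparison at 0.05.

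**What to change.** Replace the Bonferroni sentence with a stated decision rule, for example: *Consistent betterment will be declared only if every post-baseline yearly comparison of the late-stage rate favours the intervention arm at two-sided 0.05; because all must succeed, no multiplicity correction is applied. The baseline comparison is descriptive. Any claim about a single year will be tested by Holm's step-down procedure at the end of the study.*

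The text should also say whether each yearly comparison uses that year's cases only or all cases to date, since the power differs.

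The cost is a few sentences and no new data. The drawback is that a single-year claim must wait until all yearly p-values are available, and a year significant at 0.05 alone cannot be claimed unless it passes Holm.
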